##### Objective 1.B and Analysis Plan

The second analyses will be a binary variable for having, or not having, a new diagnosis of chronic hypertension during the prenatal period prior to 20 weeks of gestation. A logistic regression will be used to model the probability of being diagnosed with a new case of chronic hypertension during the prenatal period by study group. Regression coefficients with their respective *p*-values, and odds ratios with confidence intervals will be reported. 

#### 2.6.2. Research Objective 2

##### Independent Variables and Covariates

The independent variable of interest for research objective 2 will be a group variable. Participants will be randomized to one of two groups: the intervention group (digital platform with RBPM and cultural tailoring) or comparison (digital platform with RBPM but no cultural tailoring). The covariates will be the age at enrollment in years, race, ethnicity, health insurance type (e.g., Medicaid, commercial, HMO), gestational age at first visit, and total number of prenatal visits. 

##### Objective 2 and Analysis Plan

The outcome, a count variable, will be defined as the total number of recorded blood pressure readings during the prenatal period. A Poisson or Negative Binomial regression will be used to model the number of recorded blood pressure readings during the prenatal period. Interactions between the study group and race will be tested. Significant interactions between a group and race would indicate that the effect of race differed between the study groups. If an interaction is statistically significant, predicted effects with 95% confidence intervals for race by study group will be provided. Regression coefficients with *p*-values from the model will be reported.

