### 2.3. Planned Analysis: Time to Diagnosis of Hypertensive Disorders of Pregnancy

A planned analysis will be conducted, with the aim of completing the research objectives, sequentially in two phases. The first research objective will be completed as phase 1 using a time-to-event strategy and intent to treat. In this phase, we will evaluate the days to diagnosis of HDP when using the digital platform, with an active comparison group. The comparison group will receive a digital platform that offers educational content but not RBPM. Patients will be assigned 1:1 using a random number generator to either the intervention (digital platform plus RBPM) or active comparison (digital platform). The hypotheses are the following:Diagnosis of previously unrecognized chronic hypertension will increase with use of RBPM.RPBM and use of the digital platform will decrease the days to diagnosis of HDP.RBPM will decrease the time to diagnosis for all users regardless of demographic characteristics.

When phase 1 is completed, our team will incorporate culturally responsive social identification strategies to increase the engagement among Black patients. The content for cultural tailoring will be developed during phase 1 under a separate protocol not described here. The second research objective will be achieved by evaluating this tailoring in a randomized controlled trial as a second phase. The hypotheses are the following: Cultural tailoring will promote social identification and mediate treatment effects on the time to diagnosis of HDP among Black users, narrowing the equity gap in outcomes.Cultural tailoring will improve the perceived quality of care, reduce stress, and improve social support. These benefits will result in additional improvements in perinatal outcomes, such as fewer preterm birth and depression symptoms.

We further anticipate that social identification will create a consistent “brand” for the program (common desirable features, consistent imagery, look and feel) and will affect the time to diagnosis of HDP outcomes [38]. Recognition of the intervention and its tailored features will promote engagement and participation.

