### 2.4. Outcome Measures

The planned primary outcome is the time to diagnosis of HDP. Planned secondary outcomes include an improvement in the perceived quality of care and reduced maternal stress. Additionally, we will measure the effect of cultural tailoring and its associated impact on health equity. While this study is not powered to detect differences in the rates of severe maternal morbidity, we will evaluate this outcome as an investigational hypothesis. 

We have selected biometric, behavioral, and social identification measures that are linked to our conceptual framework and hypotheses. EHR review will provide information on the diagnosis and timing, gestational age at delivery, mode of delivery, maternal comorbidities, and participation in postpartum care. The study instruments will be applied after consent and before enrollment, during pregnancy as specified, and at six to eight postpartum.

Blood pressure. Blood pressure will be taken using the internet-enabled blood pressure equipment provided, which will be linked to the digital platform and integrated with the EHR. These devices are calibrated and tested for consistency with hospital-based medical equipment. All recorded values will be included from the first prenatal visit to 8 weeks postpartum for research objectives 1 and 2. 

Laboratory values. The results of laboratory testing used to diagnose preeclampsia will be extracted from the EHR, including the complete metabolic panel, urine protein–creatinine ratio, and other data for research objectives 1 and 2. 

Quality of Prenatal Care Questionnaire [39]. The QPCQ is a reliable and validated instrument developed to assess the perceived quality of prenatal care. Reported Cronbach’s alpha = 0.96 and inter-item correlation coefficient = 0.88. This will be completed once each trimester for research objectives 1 and 2. 

Perceived Prenatal Maternal Stress Scale (PPNMSS). This validated instrument consists of 28 items organized as four sub-scales of perceived social support, pregnancy-specific concerns, intimate partner interaction, and economic matters [40]. Cronbach’s alpha = 0.83, with an inter-item correlation coefficient of <0.9. For research objectives 1 and 2, the PPNMSS will be completed once each trimester. 

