Social identification. Brand equity is a term used to broadly define attitudes, perceptions, and connection that users attribute to a particular item or product. It has been successfully validated using a 16-item Likert scale reflecting four core constructs (loyalty, popularity, awareness, personality) as part of anti-smoking social marketing campaigns [41]. This scale will be adapted to measure social identification as part of research objective 2 and completed in the third trimester. 

Edinburgh Postnatal Depression Scale (EPDS). The EPDS is a validated 10-item screening assessment for depression symptoms during the perinatal period [42]. It also contains a sub-scale for anxiety. This scale has been proven to be highly sensitive and specific to both depression and change in depression over time (83.8% and 74.7%, respectively). For research objectives 1 and 2, all EPDS scores will be sourced from the medical record. The health system protocol is to complete the EPDS at each prenatal and postpartum visit. 

Uptake and Exposure. The digital platform will capture data on all aspects of user engagement, including content accessed by gestational age and postpartum stage, frequency of use, and duration (time) of each user session. These detailed usage data measure exposure and uptake for both research objectives. 

Process measures. The time from enrollment, first user activity, and number of RBPM entries will be included as measures for research objectives 1 and 2. 

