### 2.6. Analysis

The primary goal of the analysis will be to evaluate research objectives 1 and 2. For research objective 1, demographic data will be compared for the intervention and active comparison group. Time-to-event analysis will be used to compare the outcomes between these groups. We also will compare the total number and timing of blood pressure readings. For research objective 2, the analysis will focus on the mediation effects of social identification on health equity. Figure 4 illustrates the planned analyses for the primary outcome.

#### 2.6.1. Research Objective 1

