**Figure 4 ijerph-21-00603-f004:**
[figure not shown]
Three primary analyses are planned to accomplish research objectives 1 and 2.

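### Objective 2 is hypothesised as time to HDP diagnosis in Black users, mediated by social identification, but its only analysis plan models a count of blood pressure readings

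*Protocol article*

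**What the plan says.** All references are to the Protocol article.

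- **Hypotheses (section 2.3).** The first for phase 2 is: "Cultural tailoring will promote social identification and mediate treatment effects on the time to diagnosis of HDP among Black users", with a narrower equity gap as the result. The second is: "Cultural tailoring will improve the perceived quality of care, reduce stress, and improve social support", with later gains in preterm birth and depression symptoms.
- **Primary outcome (section 2.4).** "The planned primary outcome is the time to diagnosis of HDP". No different primary outcome is given for phase 2.
- **Announced analysis (section 2.6).** For objective 2, "the analysis will focus on the mediation effects of social identification on health equity".
- **Mediator (section 2.4).** A 16-item brand equity scale is the instrument: "This scale will be adapted to measure social identification as part of research objective 2 and completed in the third trimester".
- **Specified analysis (section 2.6.2).** The plan for this objective reads: "The outcome, a count variable, will be defined as the total number of recorded blood pressure readings during the prenatal period". The model is Poisson or negative binomial regression, and interactions of study group with race are tested.
- **Figure 4 caption.** "Three primary analyses are planned to accomplish research objectives 1 and 2". The three analyses described in the text are 1.A (Cox, HDP diagnosis), 1.B (logistic, new chronic hypertension) and the objective 2 count model.

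**The concern.** The specified analysis and the hypotheses concern different quantities. A group-by-race interaction on reading counts asks whether tailoring changes monitoring activity differently by race. That is effect modification of an engagement measure. It contains no diagnosis time, the social identification score does not enter it, and it yields no indirect effect. The outcomes of the second hypothesis are absent too.

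A count is also an uncertain stand-in for earlier diagnosis. The Figure 2 caption says that how often a patient monitors depends on that patient's diagnosis. A diagnosis can therefore change the later number of readings, and more readings need not mean an earlier diagnosis.

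At stake is what a 24-month randomised phase can conclude. As written, it could report a positive result on readings while its equity hypothesis, the reason for the phase, is never estimated.

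**Working it through.** **Step 1: match each hypothesised element to the section 2.6.2 model.**

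| Element | Where stated | In the objective 2 model? |
|---|---|---|
| Time to HDP diagnosis | 2.3, 2.4 | No; the outcome is a count of readings |
| Effect among Black users | 2.3 | Only for the count, through group by race |
| Social identification score | 2.3, 2.4, 2.6 | No |
| Mediated (indirect) effect | 2.3, 2.6 | No |
| Quality of care, stress, social support | 2.3 | No |
| Engagement by race | 2.1, 2.3 (as a pathway) | Yes |

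Section 2.7 adds that readings and activity will be correlated with the medical record. That is an observational association. It is neither a mediation analysis nor a randomised comparison of diagnosis times.

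**Step 2: reproduce the plan's sample size (section 2.5).** Inputs: hazard ratio (HR) 1.4, equal allocation, two-sided 0.05, power 80%, event probability 15.9%.

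- Events = (1.960 + 0.842)² / (0.25 × (ln 1.4)²) = 277.3
- N = 277.3 / 0.159 = 1744.1, rounded up to 1745

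The stated 1745 is reproduced exactly. The grouping variable in that calculation is RBPM versus no RBPM, the phase 1 contrast. It covers neither the count model nor a phase 2 test of diagnosis time.

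**Step 3: power if objective 2 is analysed as hypothesised.** The article gives no separate phase 2 sample size or effect size. Assumptions: 1745 participants in phase 2, 35% Black (section 2.5 says over 35%), 15.9% events in every group, HR 1.4 carried over from phase 1.

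- Black participants: 1745 × 0.35 = 611; events: 610.75 × 0.159 = 97.1
- Group effect in Black participants: SE of log HR = √(4/97.1) = 0.203; power = Φ(0.3365/0.203 − 1.96) = 38%
- HR detectable with 80% power: exp(2.802 × 0.203) = 1.77
- Interaction (ratio of HRs 1.4): events in other participants = 277.5 − 97.1 = 180.4; SE = √(4/97.1 + 4/180.4) = 0.252; power = Φ(0.3365/0.252 − 1.96) = 27%

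**Step 4: range.** Section 2.5 says that HDP is more common at the site than nationally, without a figure, so event rates of 15.9% to 25% and Black shares of 35% to 40% were tried.

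| Event rate | Black share | Events in Black participants | Power, Black participants | Power, interaction |
|---|---|---|---|---|
| 15.9% | 35% | 97.1 | 38% | 27% |
| 15.9% | 40% | 111.0 | 43% | 28% |
| 20% | 35% | 122.2 | 46% | 32% |
| 20% | 40% | 139.6 | 51% | 34% |
| 25% | 35% | 152.7 | 55% | 39% |
| 25% | 40% | 174.5 | 60% | 41% |

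For 80% power in Black participants at HR 1.4, the total needed is 1744.1 / 0.35, or about 4,980, at 15.9% events and 35% Black, and 2774 at 25% and 40%. Section 2.5 implies about 3000 × 0.60 = 1800 enrolled per 24 months.

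**The case against.** Four points can fairly be made for the plan.

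- **Engagement is part of the stated mechanism.** Sections 1, 2.1 and 2.3 expect tailoring to raise engagement among Black patients and thereby effectiveness. This stands: the count model addresses a stated intermediate step and is worth keeping. It does not reach the end of the pathway that the hypothesis names.
- **A full analysis plan may hold the Cox and mediation models.** Possibly so. But the article does not leave the objective 2 outcome open; it fixes one that differs from sections 2.3, 2.4 and 2.6. Extra models elsewhere would not reconcile those sections.
- **The contradiction could be resolved the other way,** by restating objective 2 as an engagement trial. That is legitimate, provided that the hypothesis and the permitted conclusions change with it.
- **The hypothesised analysis is weakly powered.** True, and it must be disclosed. Low power does not make the count a test of diagnosis time.

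Two stronger readings are not supported. A reader might infer from the Figure 4 caption that three primary outcomes are each tested at 0.05 without error control. The caption speaks of analyses and belongs to a figure not shown; section 2.4 names one primary outcome, objective 1.A alone calls its outcome primary, and 1.B is introduced as the second analysis. At most the caption wording is loose.

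A reader might also infer that any mediation model here would have its time order wrong. Readings and the diagnosis clock do start at the first prenatal visit, before the third-trimester scale, but the article gives no distribution of diagnosis times. The supportable statement is that some readings and diagnoses may precede the score.

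**Conclusion.** The contradiction is in the text and does not depend on any calculation. The sole objective 2 analysis plan estimates differential engagement, while the objective is framed as time to HDP diagnosis in Black users, mediated by social identification. No result from the count model could support a claim about diagnosis time, mediation or a narrower outcome gap.

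The power figures show the consequence of analysing the stated hypothesis: 38% in Black participants (38–60% over the range) and 27% for the interaction (27–41%). They rest on an assumed phase 2 size of 1745 and an HR of 1.4 that the article states only for RBPM versus no RBPM. They do not show an error in 1745, which is correct for its own purpose. Objective 1 and its sample size are unaffected.

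**What to change.** In section 2.6.2:

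1. **Primary.** Add the objective 1.A Cox model of time to HDP diagnosis as the phase 2 primary analysis, with group, race and their interaction, and report the group effect in Black participants. Keep all randomised participants from time zero. Do not restrict to diagnoses made after the social identification score, because that selects on a post-randomisation condition.
2. **Secondary, engagement.** Keep the reading count and its group-by-race interaction.
3. **Secondary, mediation.** Prespecify a mediation analysis using the social identification score, and state that the third-trimester score may follow some readings and diagnoses. Giving the scale earlier as well, in the existing trimester survey, would reduce this.
4. **Power.** State that 1745 was computed for RBPM versus no RBPM, and report phase 2 power with its assumptions, as in the working above.

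The alternative is to keep the count as primary and restate the objective 2 hypothesis and conclusions as engagement only.

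The primary change uses data already collected and costs analysis work; an earlier scale adds 16 items to a survey already given each trimester. The real cost is an openly stated loss of power. Phase 2 starts only after phase 1 is complete, so the change can be made before phase 2 enrolment.

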### 2.5. Sample Size and Recruitment

The sample size was calculated using PROC POWER in SAS for a two-sided Score test in the Cox proportional hazard regression of the time to diagnosis of an HDP in the study group, with a binary variable taking on the values of intervention (digital platform plus RBPM) or active comparison (digital platform). The proportion of total participants in the intervention group was set at 50%. A hazard ratio of 1.4 for the study group was used as the effect size. The overall probability that a participant would be diagnosed with an HPD was set at 15.9% [43]. The total number of subjects needed to achieve a power of 80% with a significance level of 0.05 was determined to be 1745. 

Overall, HDP affects 15.9% of delivery hospitalizations in the US [43], and the prevalence is higher among patients served by the study site. In 24 months, our system provides prenatal care to over 3000 patients. Given this patient volume and prevalence, we considered the estimated sample size feasible with a 60% enrollment rate, which is consistent with the engagement with prior research studies in our setting of similar durations. We anticipate that the required cohort for each research objective will be enrolled within the desired timeline. The total active participant enrollment time for the planned protocol will be a total of 48 months: 24 months for phase 1, and 24 months for phase 2. 

All people presenting at the study site for prenatal care will be invited to participate at their initial prenatal visit by a study research coordinator. Individuals younger than 18 years will be excluded. Over 35% of patients receiving prenatal care at our facility identify as Black, which will allow us to test for the desired sub-group effects related to social identification. Randomization will occur at the time of enrollment, and baseline measures will be completed. Participants will receive USD 25 at the time of enrollment and each time they complete study data collection (enrollment, and then each subsequent trimester and postpartum) in recognition of the additional time required to complete these study materials. Survey data will be compiled using REDcap 14.2.1, a software distributed by Vanderbilt University in Nashville, Tennessee, United States, for non-commercial secure survey data collection, at enrollment and the subsequent timepoints.

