**Figure 2 ijerph-21-00603-f002:**
[figure not shown]
Frequency of blood pressure monitoring is specific to the diagnosis of each patient and reminders are sent to aid adherence to clinical management guidance.

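### Objective 2 leaves Poisson open for the group-by-race test on reading counts that follow diagnosis-specific schedules; one negative binomial model with a robust variance would protect the error rate

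*Protocol article*

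**What the plan says.** Under Research Objective 2, participants are randomized to "the intervention group (digital platform with RBPM and cultural tailoring) or comparison (digital platform with RBPM but no cultural tailoring"). The section on the objective 2 analysis plan defines the outcome: "The outcome, a count variable, will be defined as the total number of recorded blood pressure readings during the prenatal period". It gives the model as "A Poisson or Negative Binomial regression will be used to model the number of recorded blood pressure readings during the prenatal period", adds "Interactions between the study group and race will be tested", and interprets the result: "Significant interactions between a group and race would indicate that the effect of race differed between the study groups". Predicted effects by race and arm are reported only if that interaction is significant.

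The Figure 2 caption says what drives the count: "Frequency of blood pressure monitoring is specific to the diagnosis of each patient and reminders are sent to aid adherence to clinical management guidance". The objective 2 covariates are age at enrollment, race, ethnicity, "health insurance type (e.g., Medicaid, commercial, HMO), gestational age at first visit, and total number of prenatal visits". Neither diagnosis nor monitoring schedule is among them.

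Section 2.5 supports the subgroup question with the statement "Over 35% of patients receiving prenatal care at our facility identify as Black". The article gives no mean, variance or dispersion for reading counts and no separate sample size for phase 2.

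**The concern.** The hypothesis of interest is that the group-by-race ratio of mean readings equals 1. A model-based test adds a second condition: the variance must equal the mean (Poisson) or follow mean plus dispersion times mean squared (negative binomial). If that condition fails, the standard error is wrong, and spread between women can look like an interaction or hide one.

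The article's own design gives reason to doubt the condition. Women asked to measure at different frequencies produce a mixture of counts, before any personal difference in adherence, and the mixture stays in the residual because no covariate describes it. The analysis plan written out for objective 2 rests its conclusion about race on this one p-value and makes the race-specific estimates depend on it. Its false-positive rate is therefore worth protecting.

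**Working it through.** **Inputs.** From the article: over 35% of patients identify as Black; total N = 1745, 15.9% event probability, two-sided test at 0.05 (all stated for objective 1). Assumed: phase 2 also has N = 1745, 1:1 allocation and two-sided 0.05, and all reading-count distributions below.

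**The article's own figure.** For the objective 1 Cox test, required events are (1.960 + 0.842)² / (0.25 × (ln 1.4)²) = 277.3. Dividing by 0.159 gives 1744.1, rounded up to 1745. The stated figure reproduces. There is no corresponding figure for objective 2.

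**Poisson, analytic.** Let φ be the residual variance/mean ratio, common to the four group-by-race cells. The model-based standard error is too small by a factor √φ, so the false-positive rate is 2 × (1 − Φ(1.96/√φ)). N cancels.

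| φ | False-positive rate |
|---|---|
| 1 | 5.0% |
| 2 | 16.6% |
| 5 | 38.1% |
| 10 | 53.5% |
| 20 | 66.1% |
| 50 | 78.2% |

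The rate reaches 50% when 1.96/√φ = 0.6745, that is φ = (1.96/0.6745)² = 8.44.

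**What φ a schedule mixture gives.** Suppose 15.9% of women record m times a base of 20 readings and counts are Poisson within each schedule. Then mean = 20 × (0.841 + 0.159m), between-schedule variance = (20(m − 1))² × 0.159 × 0.841, and φ = 1 + variance/mean.
- m = 1.5: mean 21.6, variance 13.4, φ = 1.6, rate about 12%.
- m = 3: mean 26.4, variance 214, φ = 9.1, rate about 52%.
- m = 7: mean 39.1, variance 1926, φ = 50.3, rate about 78%.

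**Simulation 1.** No tailoring effect; model with arm, race and their interaction; 1500 trials per row. Entries are the percentage of trials with interaction p < 0.05.

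| Assumed counts | Poisson | Negative binomial, model-based | Negative binomial, robust |
|---|---|---|---|
| m = 3 | 52.5 | 10.2 | 5.1 |
| m = 7 | 76.1 | 13.8 | 4.7 |
| m = 3, plus gamma dispersion 0.25 | 66.0 | 10.5 | 5.9 |
| m = 7, plus gamma dispersion 0.25 | 82.6 | 17.3 | 5.5 |
| 10% record nothing (mean 50, dispersion 0.5) | 72.9 | 1.7 | 4.9 |
| 20% record nothing (mean 50, dispersion 0.5) | 73.2 | 0.6 | 5.4 |

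For a true interaction ratio of 1.25, power with negative binomial model-based against robust standard errors is 57% against 75% when 10% record nothing, and 31% against 65% when 20% do.

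**Simulation 2.** Same null, but adjusted for gestational age at first visit and number of visits; 1000 trials per row.

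| Assumed counts | φ | Poisson | Negative binomial, model-based |
|---|---|---|---|
| Weekly, about 90% adherence | 0.3 | 0 | 0 |
| Weekly, variable adherence | 2.7 | 24.2 | 2.6 |
| Twice weekly, some early drop-off | 10 | 52.6 | 1.0 |
| Gamma overdispersion, dispersion 0.5 | 12 | 57.4 | 4.7 |
| Weekly, daily for 20–30% | 42 | 77.1 | 10.2 |
| Same, plus never-starters | 48 | 76.4 | 5.2 |
| Weekly, rare twice-daily group | 80 | 82.9 | 26.2 |

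With robust standard errors the rate was 3.8% to 5.7% for Poisson and 3.6% to 5.7% for negative binomial across all seven rows. Monte Carlo error at 5% is √(0.05 × 0.95/1000) = 0.7 percentage points.

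**The case against.** **The article does not commit to Poisson.** It names negative binomial, the usual model for overdispersed counts, and states no type of standard error. A selection rule or variance estimator may sit in an analysis plan that is not shown, and a journal article may properly leave both there. This stands: their absence is not the point. What remains is that Poisson is stated as acceptable for this outcome, and that neither named model protects the test by itself.

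**The size is assumed.** The content of Figure 2 is not available. The base of 20 and the threefold and sevenfold contrasts have no source in the article. The 15.9% is the probability of an HDP diagnosis; a schedule changed by that diagnosis would alter only later readings, so multiplying a woman's whole count overstates the mixture for her. This also stands. With a mild 1.5-fold contrast, negative binomial stays at about 5% and Poisson is at about 12%.

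**The planned covariates might absorb the spread.** Simulation 2 adjusted for the two most relevant ones, and the problem remained under the mixed schedules assumed there.

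**Stronger readings that the article does not support.** A reader might infer that the test will falsely declare an effect in most trials. That needs Poisson to be chosen and a variance/mean ratio above about 8.4, which no document supplies; the simulated rate was 24% with one weekly schedule and 0% with near-uniform adherence. A reader might infer that the false finding would be a gain in equity. The test is treated as two-sided, so about half of false rejections would suggest a wider gap. A reader might also take women who never use the cuff to be retained as zeros under intent to treat. Section 2.3 states intent to treat for phase 1 only, and the outcome is not limited to home readings, so a never-user need not be a zero.

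**Conclusion.** The concern holds in limited form. The article leaves Poisson open for a test on counts that its own design makes liable to overdispersion. If Poisson is used with model-based standard errors, even a variance/mean ratio of 2 more than triples the nominal error. Negative binomial is much safer but not secure. In Simulation 2 it was close to nominal in two scenarios (4.7%, 5.2%), conservative in three (0%, 1.0%, 2.6%) and inflated in two (10.2%, 26.2%), so the direction of its error cannot be known in advance. A robust variance kept both models near 5% throughout.

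These sizes rest on assumed count distributions and the phase 2 assumptions listed above. The point is a cheap improvement to a stated method. It does not show that the planned analysis must fail.

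**What to change.** In the objective 2 analysis plan, replace the choice between two models with one prespecified model, for example: *A log-link negative binomial regression with robust (sandwich) standard errors will be used to model the reading count; all p-values and 95% confidence intervals, including the group-by-race interaction, use the robust variance.* Drop Poisson with model-based standard errors.

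The cost is one sentence and one software option, with no new data or participants. Rate ratios keep their meaning. The downside is that intervals will be wider than model-based Poisson would show when counts are overdispersed, so significance is harder to reach.
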